**Methods::**

This is a cluster randomized controlled trial with adolescents from 7th to 9th grade in public schools from Florianopolis, Southern Brazil. After agreement, 6 schools were randomly selected to intervention or control groups (3 schools each), and all eligible students were invited to the study. The *Movimente* intervention program was performed during a school year and included 3 main components: Teacher training (including face-to-face meeting, social media platform, and handbook with lesson plans); improvements in the PA environment in school; and educational strategies. Control schools continued with their traditional schedule. Baseline (March/April 2017), postintervention (November/December 2017), and maintenance (June/July 2018) evaluations included PA and SB as primary outcomes (assessed by self-report and accelerometry). Secondary outcomes included psychosocial factors related to PA and SB (e.g., social support and self-efficacy), as well as health (e.g., quality of life and nutritional status) and education (e.g., academic achievement) outcomes. A program evaluation was performed based on the RE-AIM framework. Participants, intervention staffs, and evaluators were not blinded to group assignment, but a standardized evaluation protocol was applied independently of the trial allocation.

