### Power calculation

2.2

All sample size power calculations considered a statistical power of 80% and a 5% significance level for 2-tailed tests. An odds ratio of 2^[18]^ was considered meaningful, that is, students from the intervention group would be 2 times more likely to become active (self-report measure) compared with their peers from the control group. Considering these parameters and the sample design (RCT), a minimum sample of 517 subjects (1:1 between intervention and control groups) was estimated using the software OpenEpi.^[19]^ Because of the clustered nature of the sampling frame,^[18]^ the study sample was doubled to n = 1034 schoolchildren.

When estimating a sample size for PA as a continuous variable (self-report measure) using the software GPower 3.1, a sample of 1090 students has a statistical power to identify effect size equal to or higher than 0.17 (i.e., intervention vs control differences of 200 minutes per week in PA, the primary outcome) in scores in the adjusted comparisons between control (intervention and control) versus time (baseline and follow-up), considering the effect size found in a previous study using subjective measures.

Finally, considering the sample power for mediation analyses procedures (based on a simulation study from Fritz and MacKinnon ^[20]^), the needed sample to detect small mediation effects (standardized change of 0.14 or higher) when testing the mediating role of variables (i.e., social support for PA) in the intervention effect on primary outcomes is 539 for mediation analyses using PRODCLIN and 462 subjects for Bias-corrected bootstrap methods.^[20]^

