#### Physical activity

2.8.1

Students reported participation in a previously validated list of 22 different types of PA (with an option to add extra activities). Students reported whether they usually participate in any of the listed activities in a typical week, the weekly frequency and daily duration considering 2 different criteria: 1 list regarding leisure-time and another list considering total-time PA.^[15,36,37]^ This instrument showed high levels of reproducibility and a moderate level of reliability for PA dichotomous measurement. Validity of the tool against 24 hours recall was moderate and agreement in the 2 categories at 300 min/wk was moderate.^[36]^

Due to a limited number of accelerometer devices, a subsample was selected to objectively assess PA. In each group (intervention and control), schools with the smallest number of students were used as the inclusion criteria. Thus, 315 students were considered eligible. Of these, 156 control students were enrolled in a school from Southern region, while 159 intervention students were enrolled in a school located in Northern region. A total of 250 students (intervention = 136, control = 114) wore an accelerometer (response rate of 86.8%) at baseline. A detailed explanation was provided to students within class time. Participants were asked to wear ActiGraph accelerometers (GT3X+ and wGT3X+ ^[38]^) which have been widely used in large-scale studies to assess PA^[39]^ and validated for the pediatric population.^[40]^ Adolescents were instructed to wear the accelerometer on a belt positioned on the right hip over a 10-day period and only remove them for water-based activities and to sleep. Students who did not provide enough data (≥ 3 weekdays and 1 weekend day for at least 8 hours a day) were asked to rewear the device for 10 more days. The data were collected at 80 Hz and analyzed in epochs of 15 seconds, as recommended for the pediatric population.^[40]^ Periods of ≥60 minutes of zero values were defined as accelerometer nonwear time. Thresholds of movement counts (corresponding to moderate- and vigorous-intensity physical activity) in 15 second epochs developed by Evenson et al,^[41]^ an accurate threshold for this age group, will be used. From the data analysis, the main outcome will be average daily volume of PA (light PA and MVPA). Data from the accelerometers was transferred to the software Actilife 6.8 to perform reduction and validation procedures.^[42]^

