#### Sedentary behavior

2.8.2

Daily hours in SB on typical weekdays and weekend days were assessed with the following items: television viewing; virtual games (at computer and/or video-games); computer use (excluding games activities); and cell phone use (when it was the sole activity being performed while seated or lying down, i.e., cell phone use while walking was not included). Moreover, participants self-reported their overall hours of SB (e.g., sitting talking with friends, playing cards, etc.), considering the sum of all items. This instrument showed significant correlation coefficients for total screen time use. Objectively assessed sedentary time was collected based on the accelerometer data. Sedentary time will be defined as < 100 counts per minute.^[41]^

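### The mediation sample size of 539 or 462 is stated for all primary outcomes, but the accelerometer primary outcomes were measured in at most 250 students

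*Protocol article*

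**What the plan says.** Section 2.2 of the Protocol article opens with a general rule: "All sample size power calculations considered a statistical power of 80% and a 5% significance level for 2-tailed tests". Two calculations follow, one for becoming active (odds ratio 2) and one for physical activity as a continuous variable. Each is marked as referring to the self-report measure.

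The third calculation concerns mediation. It targets "small mediation effects (standardized change of 0.14 or higher" and gives the sample needed to test mediators "in the intervention effect on primary outcomes is 539 for mediation analyses using PRODCLIN and 462 subjects for Bias-corrected bootstrap methods". It carries no self-report limit.

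Elsewhere the article defines the primary outcomes more widely. The abstract lists "PA and SB as primary outcomes (assessed by self-report and accelerometry". Section 2.8, on primary outcomes, describes accelerometer activity volume in 2.8.1, and 2.8.2 adds: "Objectively assessed sedentary time was collected based on the accelerometer data".

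Section 2.8.1 also restricts who was measured: "Due to a limited number of accelerometer devices, a subsample was selected to objectively assess PA". One school per arm was used, 315 students were eligible (159 intervention, 156 control), and "A total of 250 students (intervention = 136, control = 114) wore an accelerometer" at baseline.

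Section 2.12 plans total, direct and indirect effects for each outcome. The path models control for baseline values, and the significant mediators go on to a multiple-mediator model.

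**The concern.** Read together, these sections state a required size for a set of outcomes, and some of those outcomes were measured in about half that number of students. A baseline-adjusted accelerometer model cannot use more than the 250 students with a baseline measurement, and loss by the second time point can only reduce that.

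What is at stake is how the mediation results on the objective measure are read. Section 2.12 selects mediators by significance before the multiple-mediator model. With low power, most true mediators of the stated size would drop out at that step for the accelerometer outcomes. Meanwhile section 2.2 gives a size for the primary outcomes that the 999 enrolled students comfortably exceed.

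**Working it through.** **Inputs from the Protocol article**
- Two-sided 5% and 80% power; standardized effect 0.14; needed N of 539 (PRODCLIN) and 462 (bias-corrected bootstrap): section 2.2.
- Accelerometer N: 315 eligible; 250 wore a device (136 intervention, 114 control): section 2.8.1.
- Enrolled N: 999: section 2.4.

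**Assumption.** Section 2.2 does not say whether 0.14 is the size of each path or of their product. Here it is taken as a = b = 0.14 (a: intervention to mediator; b: mediator to outcome).

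**Step 1. Size comparison, with no model.**
- 250/539 = 46%; 250/462 = 54%.
- All 315 eligible students would still fall short: 315/462 = 68%; 315/539 = 58%.

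**Step 2. Reproduce the stated sizes.** Single-mediator simulation: X standardized, M = 0.14X + e, Y = 0.14M + e, no direct effect, unit residual SD, independent students, complete data.
- Product-distribution limits (PRODCLIN), N = 539: power 79.5% and 80.5% in two runs.
- Bias-corrected bootstrap (1,000 resamples), N = 462: 78.4% and 78.0% in two runs.
- Joint significance of both paths (non-central t): 80% power needs N = 528, close to 539.

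Both stated sizes are recovered to within about two percentage points of power.

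**Step 3. Same model at N = 250.**

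| Method | Power at the stated N | Power at N = 250 |
|---|---|---|
| PRODCLIN | 79.5–80.5% (N = 539) | 32.6–33.3% |
| Bias-corrected bootstrap | 78.0–78.4% (N = 462) | 43.0–46% over separate runs |
| Joint significance | 81.1% (N = 539) | 35.6% |

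With a binary arm indicator split 136/114, PRODCLIN gives 34.2%.

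**Step 4. Check by hand.** Each path has expected z = 0.14 × √250 = 0.14 × 15.81 = 2.21. Power per path is about Φ(2.21 − 1.96) = Φ(0.25) = 0.60. Both paths together: 0.60² = 0.36, in line with the 35.6% above.

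**Step 5. Path size for 80% at N = 250.** Joint power of 0.80 needs √0.80 = 0.894 per path, which is z = 1.25. The path size is then (1.96 + 1.25)/√250 = 3.21/15.81 = 0.203, against 0.14.

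**Limits of steps 3 to 5.** They treat students as independent and data as complete, so the powers are optimistic upper bounds and 0.203 is an optimistic lower bound. With one school per arm, path a in the subsample cannot be told apart from a difference between two schools. No sample-size formula for independent students repairs that.

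**The case against.** The strongest defence is that the authors meant the self-reported outcomes throughout. Both earlier calculations in section 2.2 say so, the second treats self-reported weekly minutes as the primary outcome, and the Discussion speaks of primary measures that are self-reported. On that reading 999 students exceed both figures and only a qualifier is missing. This is a fair account of what may have been intended. It does not settle the matter, because the abstract and section 2.8 put accelerometry among the primary outcomes and section 2.12 exempts no outcome from mediation.

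The defence is right on several further points, where a reader might infer more than the article supports:
- **That the protocol claims 80% power for accelerometer mediation.** It gives a needed size and openly reports the subsample and the reason for it. It nowhere says that the subsample is large enough.
- **That 539 and 462 are wrong.** They are reproduced. The fault is in their scope.
- **That 0.14 per path is the plan's own input.** It is an assumption, supported only by its reproducing both sizes.
- **That 250 is the count before invalid wear is excluded.** Section 2.8.1 describes asking students to wear the device again but does not say at which stage the 250 were counted.
- **That readers will take null accelerometer mediation as evidence against a mechanism.** This is possible but speculative, and mediation is an additional aim.

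Power for a secondary analysis could also be left to a fuller document. Here, however, the article chose to state a size, and stated it for outcomes that do not reach it.

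**Conclusion.** The point holds as a fault of scope: section 2.2 attaches 539/462 to all primary outcomes, while the accelerometer ones have at most 250 students, about half the stated need. That comparison rests on the article's own numbers alone.

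Its consequence for power rests on the assumption of 0.14 for each path, with independent students and complete data. On that basis power is at most about 33% (PRODCLIN) to 43–46% (bias-corrected bootstrap), so a true effect of the stated size would be missed more often than found. The real position is weaker still, because of clustering, loss by follow-up and the complete confounding of arm with school in the subsample. The self-reported outcomes are not affected by this point.

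**What to change.** - **Section 2.2:** limit the 539/462 statement to the self-reported primary outcomes. Add that the accelerometer subsample (at most 250 students, one school per arm) does not reach that size. If a power figure is quoted for it, give the assumed path size and present the figure only as an optimistic upper bound that ignores clustering and the confounding of arm with school.
- **Section 2.12:** label mediation on accelerometer activity and sedentary time exploratory, report estimates with intervals, and draw no conclusion about which mediators work.

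The cost is a few sentences and no new data. The downside is a less favourable claim for mediation on the objective measures.

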### Data treatment and statistical analyses

2.12

The tabulation of questionnaire data will be performed using an optical reading using the software “SPHYNX.”^[57]^ At the end of the process, the tabulation will be manually checked by 2 staff members of the Movimente study team. The management and processing of the database as well as the descriptive analyses will be performed in the statistical package “STATA Standard Edition 15.”^[58]^ Inferential analyses will be performed in both STATA and R Project for Statistical Computing 3.5.1 software.^[59]^

Descriptive analyses will be performed to describe the sample, presenting mean values for continuous variables and absolute and relative frequency for qualitative variables, both with their respective 95% confidence intervals (95% CI). Pearson *χ*^2^ tests will be used to compare sociodemographic characteristics among adolescents with valid PA accelerometer data to those without valid data.

The multilevel approach for repeated measurements will be applied through the application of generalized linear mixed models in the inferential analyses of PA and SB (primary outcomes). The models will be tested in relation to their assumptions of normality and independence of residues, as well as checked in relation to homoscedasticity. If these assumptions are not met, linear models for different families (e.g., Gamma) will be tested that are better suited to the features of the modeled variables. Transformation of non-normally distributed variables will be performed where appropriate. In addition, Akaike information criterion (AIC), and Bayesian information criterion (BIC) will be applied to evaluate models fit.

Regarding mediation, the following steps will be followed: action theory test (Pathway A: to investigate the impact of the intervention on hypothesized mediators at time 2, controlled for baseline values); conceptual theory test (Pathway B: to analyze the association between mediators and the dependent variable at time 2, controlled for group assignment and baseline values); to verify the total effect (Pathway C), direct effect (Pathway C’: analyze the effect of the intervention that is not explained by the mediators) and indirect effect (Pathway AB: the mediated effect) of the intervention for each outcome; a significance test of the mediated effect and the proportion mediated [AB/ (C’ +AB)] were calculated. Then, a multiple mediator model will be performed by including the significant mediators.^[60]^

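### The mediation sample sizes (539 and 462) carry no clustering allowance in a six-school trial, and the final mediator model keeps only mediators that tested significant

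*Protocol article*

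**What the plan says.** Section 2.2 (Power calculation) opens with a general rule: "All sample size power calculations considered a statistical power of 80% and a 5% significance level for 2-tailed tests". For the binary activity outcome, "a minimum sample of 517 subjects (1:1 between intervention and control groups) was estimated using the software OpenEpi", and because of clustering "the study sample was doubled to n = 1034 schoolchildren". For the continuous outcome, "a sample of 1090 students has a statistical power to identify effect size equal to or higher than 0.17". For mediation, relying on a published simulation study, it gives "the needed sample to detect small mediation effects (standardized change of 0.14 or higher") and states that this number "is 539 for mediation analyses using PRODCLIN and 462 subjects for Bias-corrected bootstrap methods". No ICC or clustering factor accompanies the mediation figures, and they are not compared with enrolment.

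Section 2.1 places randomization at school level. Section 2.4 reports six matched schools, three per arm, and 999 students at baseline.

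Section 2.12 names generalized linear mixed models for physical activity and sedentary behavior, then lists the mediation steps. Pathway A is the intervention's effect on each mediator. Pathway B is to "analyze the association between mediators and the dependent variable at time 2". The total, direct and indirect effects, a test of the mediated effect and the proportion mediated follow. The last step is: "Then, a multiple mediator model will be performed by including the significant mediators".

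**The concern.** Pathway A compares intervention schools with control schools. It therefore carries school-level variation just as the primary comparison does, and an indirect effect cannot be more secure than its weaker path. A mediation requirement worked out for independent students is too small in this design. A reader who sets 539 and 462 beside 999 would conclude that mediation is comfortably powered.

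The second issue is the selection rule. Keeping mediators because their estimates were large enough to be significant, and then refitting on the same data, pushes the retained effects upward.

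A smaller point is that section 2.12 speaks of time 2, while section 2.7.2 labels the visits T0, T1 and T2. Time 2 could be the second visit (T1, post-intervention) or T2 (maintenance). Section 2.1 says that control schools received the materials after the intervention period, so the choice could change what is being compared.

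The mediating role of the psychosocial and environmental variables is a declared aim in section 2.1, so these figures and this rule bear on conclusions that the trial intends to draw.

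**Working it through.** **Inputs.** From section 2.2: 80% power, two-sided 5%, standardized effect 0.14, needs 539 and 462, clustering factor 1034/517 = 2. From section 2.4: 6 schools and 999 students, so m = 999/6 = 166.5 per school. Assumed, because the article does not give them: the ICC (0 to 0.05), equal school sizes, normal-theory path statistics, 0.14 on each path, and loss to follow-up of 10% to 30%.

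**1. Reproducing the plan's figures.** With independent students each path statistic is taken as normal with mean 0.14·√N and SD 1, and the product is tested by simulation. PRODCLIN at N = 539 gives power 0.800. The bias-corrected bootstrap at N = 462 gives 0.797. Both match. If 0.14 were the mediated product (paths √0.14 = 0.374), power at 539 would be about 1.00, so 0.14 is a per-path value.

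**2. The plan's own factor.** 539 × 2 = 1078 and 462 × 2 = 924. The planned 1090 exceeds both. Enrolled: 1078 − 999 = 79 short. For the bootstrap, 924/999 = 0.925, so loss must stay below 7.5%. Assumed loss of 10/20/30% leaves 899/799/699 students. Halved, that is 450/400/350, all below 462.

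**3. Explicit ICC.** The design effect is DE = 1 + (m − 1)·ICC. At ICC 0.01, DE = 1 + 165.5 × 0.01 = 2.66 (2.655 unrounded). The last four columns give simulated power at N = 999, with DE on path A only unless stated.

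| ICC | DE | 539·DE | 462·DE | PRODCLIN | Bootstrap | PRODCLIN, 4-df t on A | PRODCLIN, DE on both paths |
|---|---|---|---|---|---|---|---|
| 0 | 1.00 | 539 | 462 | 0.986 | 0.991 | 0.892 | 0.986 |
| 0.005 | 1.83 | 985 | 844 | 0.897 | 0.935 | 0.680 | 0.808 |
| 0.006 | 1.99 | 1074 | 921 | 0.872 | 0.901 | 0.645 | 0.758 |
| 0.01 | 2.66 | 1431 | 1227 | 0.767 | 0.810 | 0.530 | 0.574 |
| 0.02 | 4.31 | 2323 | 1991 | 0.560 | 0.640 | 0.366 | 0.287 |
| 0.05 | 9.28 | 4999 | 4285 | 0.302 | 0.394 | 0.199 | 0.074 |

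The 4-df reference treats the schools as unmatched. With three matched pairs and 2 df, PRODCLIN power at ICC 0.01 is 0.329.

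**4. The ceiling with six schools.** The N columns hold school size at 166.5, so they imply more schools (1431/166.5 = 8.6). With six schools fixed, effective size is N / [1 + (N/6 − 1)·ICC], which cannot exceed 6/ICC. An effective 539 is out of reach once ICC exceeds 6/539 = 0.0111, and an effective 462 once it exceeds 6/462 = 0.0130. Even at ICC 0.01, solving for N gives 539 × 0.99/(1 − 539 × 0.01/6) = 5249 and 462 × 0.99/(1 − 462 × 0.01/6) = 1989.

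**5. Selection.** This is the mean estimated indirect effect among mediators that pass the test, divided by the true value, at N = 999. With both paths 0.14 the ratio is 1.01 (ICC 0), 1.06 (0.005), 1.15 (0.01), 1.34 (0.02) and 1.80 (0.05). With path A at 0.05 it is 1.68 even at ICC 0. Without selection the ratio is 1.00.

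**The case against.** Several points on the other side stand.

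- A reader might infer that the article declares the trial adequately powered for mediation. It does not. It gives a requirement per method, each figure is right for independent students, and the planned 1090 covers both doubled figures.
- Multiplying the whole requirement by a design effect penalizes both paths. Path B is largely a within-school association. With DE near 2 on path A only, PRODCLIN power at 999 is 0.872, so the shortfall against 1078 is not proof of inadequate power. That figure uses a normal reference for a six-school contrast, however; with 4 df it is 0.645.
- A reader might infer a single-level mediation model or a bootstrap that resamples students. Neither is stated. The bootstrap appears only as a sample-size reference, the abstract's mention of a multilevel approach can be read as covering mediation, and the detail may sit in a document not shown.
- A reader might infer that all mediated effects and the proportion mediated are inflated. In section 2.12 the single-mediator effects and the proportion mediated come first, before any selection, and are not biased by it.
- A reader might compute 1 − 0.95^7 = 0.302 as the chance of a false mediator among the seven screen-time scales. That is a worst case, needing path A null and path B clearly non-zero for all seven. With both paths null the per-test error is about 0.13%, or 1 − 0.9987^7 = 0.9% over seven.

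None of this removes the inconsistency within section 2.2 or the stated selection rule.

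**Conclusion.** The point holds in two limited parts.

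First, 539 and 462 do not deliver the 80% power that section 2.2 attributes to all its calculations, because they ignore the school clustering that the section allows for elsewhere. Whether 999 students suffice is not shown, and it depends on an ICC that the article does not give. With a normal reference and clustering on path A only, 999 is enough at very small ICCs; PRODCLIN power falls below 80% by ICC 0.01 and bootstrap power by 0.02. With small-sample degrees of freedom it falls below 80% earlier. These results rest on the assumed ICC range, equal school sizes and 0.14 on both paths.

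Second, the rule of carrying forward only significant mediators overstates the retained effects in the final multiple-mediator model. The size runs from negligible to 80% or more over the cases examined, so it is a risk of known direction but unknown magnitude.

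The documents do not support a claim of wrong stated adequacy, a student-level bootstrap, or bias in the first-stage estimates. The time 2 label is a minor wording ambiguity.

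**What to change.** - In section 2.2, restate the mediation requirement either with the clustering factor already used (1078 and 924) or, better, with an explicit ICC and six schools, since the factor of 2 has no stated ICC behind it. Say that the PRODCLIN figure so adjusted is not met at n = 999 and that mediation power is not assured.
- In section 2.12, state that the multilevel approach named for the primary outcomes also applies to pathway A, with small-sample degrees of freedom that reflect six matched schools.
- Report the multiple-mediator model with all prespecified mediators, or keep the selected model and label it exploratory.
- Replace time 2 with the defined visit label.

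The cost is mostly wording and a little extra modelling. The indirect-effect intervals will be wider and the stated power less favorable. No further data are needed.
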